### Intervention

The theoretical framework of the MAGDA-DPP intervention is based on the Health Action Process Approach (HAPA), and supported by social cognitive theory [21,22] and self-regulation theory [23-25], which has informed the structuring of the program and activities in each session. The intervention was based on the *Life!* program [26], which was previously shown to be effective in affecting change in diabetes risk factors. The theory driven components of the program were enhanced and the content of sessions tailored to reflect the issues that previous work has shown to be of relevance to this population (for example, sleep deprivation, post-natal depression). The intervention delivery is driven by a facilitator’s manual that outlines the core content and behavioral change processes to be used in each session of the program. Fidelity of the program will be established by assessment of the audio recordings when the facilitator is delivering the sessions.

The intervention group will be offered a series of six face-to-face sessions delivered by trained healthcare professionals, with two additional follow-up telephone calls at a later stage. Table 2 summarizes the core curriculum of the sessions. The first session will be an individual session carried out in the woman’s home, nominated community health center or Aboriginal health center. The initial session will be followed by five group sessions held at two week intervals and two subsequent phone calls at three and six months after the final group session. Each group session will be two hours long with up to 15 women per group. The control group will continue with usual care and be offered the intervention program after 12 months subject to timing or availability of MAGDA-DPP courses. An indicative timeline from recruitment to completion of the follow-up is illustrated in Figure 2.

**Table 2 T2:** MAGDA-DPP core curriculum and key contents of the six sessions and two follow-up telephone calls

**Session**	**Topics covered**
Individual session (delivered in participant’s home at >3 months postpartum)	Introduction to DPP
	Assessment of personal risk of developing T2DM
	Highlight the five program goals:
	• Reduce weight by 5%
	• Reduce total fat intake to < 30% daily energy intake
	• Reduce saturated fat intake to < 10% daily energy intake
	• Increase fiber intake to > 15 g per 1000 kcal
	• Increase physical activity to at least 30 minutes moderate intensity physical activity on at least 5 days per week
	Build commitment to attend the program by discussed perceived benefits and importance of attending
	Establish personal weight goal (current weight minus 5%) for the after 3 months
	Set physical activity goal
Group session 1 (held in community venue within 1 month of individual session)	Background to the program
	What is diabetes?
	Physical activity goal-setting: review of progress with goal set at the individual session
	Fighting fat: saturated fat
	• Benefits of reducing saturated fat intake
	• Identify common sources of saturated fats in foods and from food labels
	• Practice modifying foods to reduce saturated fat content
	Saturated fat goal-setting
Group session 2 (held in community venue 2 weeks after Group session 1)	Review goals set, and set new activity goal
	Fighting fat: total fat
	• Benefits of reducing total fat intake
	• Identify sources of dietary fat
	• Self-assessment of current total fat intake
	• Practice modifying foods to reduce total fat content
	Weight management
	Total fat goal-setting
Group session 3 (held in community venue 2 weeks after Group session 2)	Review goals set, and set new activity goal
	Filling up on fiber
	• Benefits of increasing fiber intake
	• Goals for daily fiber intake
	• Self-assessment of current fiber intake
	• Identify high-fiber foods
	• Identify meal plans that are high in fiber
	Family healthy eating (part 1)
	• Healthier shopping activity
	Healthy eating goal-setting (1)
Group session 4 (held in community venue 2 weeks after Group session 3)	Review goals set, and set new activity goal
	Family healthy eating (part 2)
	• Healthier family meal-planning
	• Dealing with barriers to making healthier choices
	Mindful eating
	Managing sleep
	• Importance of good family sleep patterns
	• Ways to improve sleep
	Healthy eating goal-setting (2)
Group session 5 (held in community venue 2 weeks after Group session 4)	Review goals set and set new activity goal
	Stress
	• Impact of stress on feelings and behaviors and health
	• Identify sources of stress
	• Identify unhelpful stress-management strategies
	• Discuss more helpful ways of managing stress
	Depression
	• Identifying depression
	• Impact of depression
	• Identifying ways to manage depression
	• Resources available for support
	Relapse prevention
	• Weight and energy balance
	• Managing relapses
	• Key strategies for maintaining a healthier lifestyle
	Long-term goal-setting
	• Action-planning
	• Problem-solving
	• Rewards
Telephone follow-up 1 (3 months after Group session 5)	Review of progress
Telephone follow-up 2 (6 months after Group session 5)	Review of progress

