### Sample size and power calculation

For the estimation of sample size for two groups, using a two-sided 5% significance level and 80% power, the total number required will be 430 (215 in each arm). The sample size calculation was based on the observed mean change in FPG over 12 months in the Greater Green Triangle Diabetes Prevention Program (GGT DPP) study [36] and is powered to detect an effect size of 0.27 (assuming mean difference between intervention and control groups of 0.14 mmol/L and within group standard deviation of 0.5 mmol/L). To allow for an estimated attrition rate of up to 25% (estimate based on the GGT DPP), we will require a total sample of 574 (287 in each arm). This sample size will provide sufficient power to also analyze changes in weight and waist circumference. The intention-to-treat (ITT) principle will be adhered to, and sensitivity analysis will also be carried out.

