### Data analysis

Analyses will be performed using STATA version 12 or later (Stata Corp., College Station, TX, USA) and the ITT principle will be adhered to. Baseline characteristics will be compared between the intervention and control groups using χ^2^ tests, independent t-tests, and/or the Wilcoxon rank-sum test, as appropriate. Primary and secondary outcome (as described above) will be evaluated using mixed models, treating ‘group’ as a between-subject factor, and ‘time’ as a within-subject factor. Two-sided tests will be used, with a level of *P*<0.05 determining statistical significance.

A separate and parallel economic evaluation protocol will be described elsewhere.

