### Trial status

Recruitment in Melbourne (Victoria) commenced at The Royal Women’s Hospital in January 2011, followed by Sunshine Hospital in November 2011 and in Adelaide (South Australia) at Lyell McEwin Hospital in January 2012. By June 4, 2013, 1,517 women diagnosed with GDM have been approached during their clinic appointments at the above three hospitals. Of these, 340 women have given written consent, 219 have not yet returned their consent form, 701 have declined to participate in the study and 257 were ineligible. Recruitment, both retrospectively and prospectively, at Women’s and Children’s Hospital and Flinders Medical Centre in Adelaide is expected to commence in mid-2013.

Baseline testing commenced in July 2012 in Melbourne (Victoria) and March 2013 in Adelaide (South Australia). By June 4, 2013, 134 women had been randomized to either the intervention or the control group. The first MAGDA-DPP intervention group started in November 2012, and there have been six groups, four in Melbourne (Victoria) and two in Adelaide (South Australia), initiated since then.

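### The sample size makes no allowance for correlation between women in the same course, and the stated mixed model names no course term; if that correlation is positive, FPG power is below 80% and the 5% test is too liberal

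*Protocol article*

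**What the plan says.** All places are in the Protocol article.

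- **Randomization:** women are allocated individually, in blocks, from separate lists for each venue or stratum.
- **Intervention:** one individual session is followed by five group sessions. On these it says "Each group session will be two hours long with up to 15 women per group". The control arm continues with usual care.
- **Sample size and power calculation:** "using a two-sided 5% significance level and 80% power, the total number required will be 430 (215 in each arm"). The calculation is "powered to detect an effect size of 0.27". The figures behind that standardised effect, for the change in FPG over 12 months, are then given in brackets: "assuming mean difference between intervention and control groups of 0.14 mmol/L and within group standard deviation of 0.5 mmol/L". The only inflation is for dropout: "To allow for an estimated attrition rate of up to 25" per cent, which leads to 287 per arm and 574 in total. No ICC, course size or design effect is mentioned.
- **Data analysis:** "Primary and secondary outcome (as described above) will be evaluated using mixed models". The between-subject factor is called *group*, which here means trial arm; the within-subject factor is time. No term for course or facilitator is named.
- **Trial status:** by June 4, 2013, 134 women had been randomised. Of the courses, it reports that "there have been six groups, four in Melbourne (Victoria) and two in Adelaide (South Australia), initiated since then".

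**The concern.** Women in one course share a facilitator, a venue, peers and repeated joint goal review. Their outcomes may therefore resemble each other more than those of women in different courses. This can happen only in the intervention arm, which makes the trial partially nested.

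If the correlation is positive and the analysis ignores it, the standard error of the arm difference is too small. The nominal 5% test then rejects too often, in the direction of declaring a difference. Separately, a sample size derived under independence gives less power than stated once the standard error is computed correctly.

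The sample-size statement is complete in the article and has no room for such an allowance. The model statement is less complete, but the factors it names are consistent with the independence assumed in the sample size.

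**Working it through.** **1. Reproduce the stated size.** Inputs from the sample size section: two-sided 5%, 80% power, effect size d = 0.27.

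n per arm = 2(1.960 + 0.842)² / 0.27² = 215.3, against 215 stated. Power at 215 per arm = Φ(0.27/√(2/215) − 1.960) = Φ(0.839) = 79.9%. Attrition: 430/0.75 = 573.3, hence 574.

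The stated figures follow from full independence plus 25% attrition. At d = 0.27 nothing is left over for clustering.

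**2. Analysed course size, m.** The stated maximum is 15. The Trial status figures suggest about 134/2/6 ≈ 11 starting a course, if the arms are equal and every intervention woman had been placed. The 215 is a number after attrition, so m must be as well: 11 × 0.75 = 8.25 and 15 × 0.75 = 11.25, assuming dropout is spread evenly over courses.

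**3. Formulas, with the design effect in one arm only.**

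- DE = 1 + (m − 1) × ICC in the intervention arm; 1 in the control arm.
- True variance over assumed variance = (1 + DE)/2.
- Type I error if clustering is ignored = 2[1 − Φ(1.960/√((1 + DE)/2))].
- Power with the correct standard error = Φ(d/√((1 + DE)/215) − 1.960).

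Example, m = 11.25 and ICC 0.05: DE = 1 + 10.25 × 0.05 = 1.5125. The variance ratio is 2.5125/2 = 1.256 and the standard error ratio 1.121. Type I error = 2[1 − Φ(1.749)] = 8.0%. Power = Φ(0.27/√(2.5125/215) − 1.960) = Φ(0.538) = 70.5%.

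**4. Results over an assumed ICC range** (d = 0.27, 215 per arm; the first figure in each cell is for m = 8.25, the second for m = 11.25):

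| ICC | True SE / assumed SE | Type I error | FPG power |
|---|---|---|---|
| 0.01 | 1.02, 1.03 | 5.4%, 5.6% | 79%, 78% |
| 0.02 | 1.04, 1.05 | 5.8%, 6.2% | 77%, 76% |
| 0.05 | 1.09, 1.12 | 7.1%, 8.0% | 73%, 70% |
| 0.10 | 1.17, 1.23 | 9.3%, 11.1% | 67%, 62% |

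These use normal quantiles. Small-sample degrees of freedom for a limited number of courses would lower the power somewhat further.

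**5. The plan's own slack.** The stated difference and SD give 0.14/0.5 = 0.28, not 0.27. At 0.28 and 215 per arm, power under independence is 82.7%. It stays at 80% while DE ≤ 215 × 0.28²/(1.960 + 0.842)² − 1 = 1.148. That is an ICC of 0.148/10.25 ≈ 0.014 for m = 11.25, or 0.148/7.25 ≈ 0.020 for m = 8.25. Type I error does not depend on d, so this slack does not protect it.

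**The case against.** The strongest objection is that half of the point rests on silence. The article says mixed models and names two factors, but does not list random effects. A full analysis plan, not shown here, could contain a course effect. A reader might infer that the model treats all women as independent, but the article does not say so. This objection stands for the analysis. It does not reach the sample size, whose derivation is stated in full.

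A reader might also infer that the standard errors are certainly too small and that 80% power is certainly missed. The documents do not support that either, because no ICC is given. At an ICC of 0.01 the loss is one to two percentage points, and with 0.14/0.5 = 0.28 power would still be above 80%.

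Larger losses can be produced by pairing 215 analysed women with full courses of 15: at an ICC of 0.10 this gives a type I error of 13% and power of 57%. That combination mixes a number after attrition with a course size before attrition, so those extremes should not be quoted.

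The 80% figure concerns FPG only. The article gives no effect size or SD for weight or waist circumference, so a power shortfall cannot be calculated for them.

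Finally, randomisation uses separate lists by venue or stratum. Correlation that merely reflects venue is shared by controls in that stratum and should not count as inflation in one arm. This is correct, but it leaves the correlation from shared peers and facilitator, which controls do not have.

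**Conclusion.** The point holds in conditional form. Delivery is grouped in one arm, the stated sample size contains no allowance for it, and the stated model names no course term. Following the article as written would understate the standard error of the arm difference for any positive within-course ICC, and FPG power at effect size 0.27 would fall below 80%.

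How much depends on a quantity the article does not give. Over an assumed ICC of 0.01 to 0.10, type I error runs from 5.4% to 11.1% and FPG power from 79% to 62%. The range rests on 215 analysed per arm, 8 to 11 analysed women per course, and the same total SD in both arms. At the low end the effect is minor; from an ICC of about 0.05 it is material. The slack from 0.28 covers power only up to an ICC of about 0.01 to 0.02.

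**What to change.** - **Data analysis:** add to the primary mixed model a random effect for course in the intervention arm only. Treat controls, and intervention women never placed in a course, as singletons, so that everyone randomised stays in the intention-to-treat comparison. Use small-sample degrees of freedom: at 11 to 15 women starting each course, 287 women form only about 19 to 26 courses (287/15 and 287/11). If a fuller analysis plan already has such a term, the article should say so.
- **Data collection:** record the course to which each intervention woman is allocated. The article does not say that this is done, though the courses are scheduled and it should be easy to obtain.
- **Sample size and power calculation:** restate the FPG power for 215 analysed per arm under a declared ICC and analysed course size, preferably over a short range, and use one effect size (0.27 or 0.28) throughout.

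The cost is one model term, one recorded variable and a revised power statement. Intervals will be slightly wider and the stated power less favourable. No extra enrolment is needed to make the change. With 134 women randomised at the time of writing, it can still be specified in advance of the results.

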**Figure 2 F2:**
[figure not shown]
Indicative timeline from recruitment to completion of follow-up.

At the first individual session, the participant will be provided with an intervention program handbook. The intervention program aims to encourage participants to achieve the following five goals: (1) reduce fat intake (no more than 30% of energy from fat); (2) decrease saturated fat intake (no more than 10% of energy from saturated fat); (3) increase fiber intake (at least 15 g per 1000 kcal); (4) increase physical activity (at least 30 minutes of moderate exercise per day); and (5) reduce body weight (at least 5% of body weight reduction within 12 months).

### Outcome assessment

At baseline and completion of the study (12 months after baseline), primary (changes in diabetes risk) and secondary (changes in cardiovascular disease risk factors, psychosocial and quality of life measurements) outcome will be assessed.

#### Primary outcome

The primary outcome is the change in diabetes risk, as determined by changes in FPG, weight, or waist circumference. A statistically significant change in any one of these three endpoints will be regarded as evidence of a change in diabetes risk. No adjustments to significance levels will be made for multiple testing. These co-primary outcome will be assessed at baseline and 12 months for all women, and additionally at 3 months (or as soon as possible after the final group session) for the intervention participants only.

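### One conclusion about diabetes risk rests on any one of three unadjusted 5% tests, so its overall false-claim rate is about 11 to 14%, two to three times the per-test level

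*Protocol article*

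**What the plan says.** The Primary outcome section of the protocol article defines the outcome through three measurements: "The primary outcome is the change in diabetes risk, as determined by changes in FPG, weight, or waist circumference". The decision rule follows: "A statistically significant change in any one of these three endpoints will be regarded as evidence of a change in diabetes risk". The next sentence reads "No adjustments to significance levels will be made for multiple testing". The section calls the three endpoints co-primary.

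The Data analysis section sets the level for each test: "Two-sided tests will be used, with a level of" P<0.05. It gives no hierarchy, gatekeeping or division of the 5% among the endpoints, and the article gives no reason for leaving the tests unadjusted.

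The sample size section works from FPG: "The sample size calculation was based on the observed mean change in FPG over 12 months", and the trial "is powered to detect an effect size of 0.27" at two-sided 5% and 80% power. It adds, without figures, that the sample is also sufficient for weight and waist circumference.

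**The concern.** Leaving several primary endpoints unadjusted can be defended when each supports its own separate statement. Here the three tests feed one statement, that diabetes risk has changed, and a single success is enough. Each test holds its 5% level, but the combined statement does not. The co-primary label does not help, because the rule asks for any one endpoint and not for all three.

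What is at stake is the trial's headline answer. The programme could be reported as changing diabetes risk because waist circumference alone reached P<0.05, while FPG, the endpoint behind the sample size, showed nothing. That is a realistic outcome: the trial is open, and weight loss is itself one of the programme's five goals.

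**Working it through.** **Inputs from the protocol article.** Three endpoints, any-one rule, no adjustment (Primary outcome). Two-sided 0.05 per test (Data analysis). 215 per arm evaluable, effect size 0.27, 80% power, 25% attrition, 287 per arm recruited (Sample size and power calculation). The article gives no correlations between endpoints, so those below are assumptions.

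**1. The plan's own sample size.**
- n per arm = 2(1.960 + 0.842)² / 0.27² = 215.4, rounded up to 216. The article says 215, which gives 79.9% power.
- Attrition: 215 / 0.75 = 286.7, so 287 per arm and 574 in total, as stated.

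The stated size is thus a calculation for one endpoint tested at the full 5%.

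**2. Overall false-claim rate when no endpoint is affected.**
- Independent endpoints, either direction: 1 − 0.95³ = 14.3%.
- Independent endpoints, false benefit only: 1 − 0.975³ = 7.3%, against 2.5% for one test.

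For correlated endpoints, three correlated standard normal test statistics were simulated, and draws with at least one beyond 1.96 were counted:

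| Assumed correlation, weight with waist | Assumed correlation, FPG with each | Either direction | False benefit only |
|---|---|---|---|
| 0.7 | 0.2 | 12.8% | 6.4% |
| 0.8 | 0.3 | 12.1% | 6.1% |
| 0.9 | 0.4 | 11.2% | 5.6% |

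At the more extreme pair 0.95 and 0.5, the either-direction rate is still above 10%. It would fall to 5% only if all three tests were perfectly correlated.

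**3. What adjustment does to the error rate.** Holm's first step is Bonferroni, 0.05 / 3 = 0.0167. If the endpoints are independent, the chance of any false claim is 1 − (1 − 0.0167)³ = 4.9%. It is at most 5% whatever the correlations.

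**4. What adjustment costs FPG.** Power = Φ(0.27 × √(215/2) − z), where 0.27 × √107.5 = 2.799.
- At 0.05: Φ(2.799 − 1.960) = Φ(0.839) = 79.9%.
- At 0.0167: Φ(2.799 − 2.394) = Φ(0.405) = 65.7%.

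The second figure is the worst case for Holm. It applies when FPG must pass the strictest step. If weight or waist has already passed, FPG faces 0.025 or 0.05.

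**The case against.** The strongest reply is that the absence of adjustment is declared. The 5% in the sample size section is correct for the FPG calculation, the Data analysis section gives 5% per test, and the article nowhere asserts a 5% family-wise rate. This is right: it is a disclosed design choice and not an internal contradiction. But disclosure does not control the error of a conclusion drawn from the best of three tests. Nor can the point be left to an unseen analysis plan, because the article fixes the rule itself.

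A second reply is that 11 to 14% counts false claims of harm as well as of benefit. That also stands, and both figures are given above. The relative excess is the same, because the comparator for benefit alone is 2.5%.

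Three stronger readings might be inferred, and the article does not support them:

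- **A significantly worse FPG would count as success.** The rule's sentence names no direction. However, the section introducing the MAGDA study speaks of favorable changes, and the abstract and main Discussion both ask about a reduction in risk. The intended direction is clear; the sentence is loosely worded.
- **Change over time within an arm would be enough.** The objectives are relative to usual care, the sample size uses a difference between arms, and the mixed model has group as a between-subject factor. The contrast is between arms.
- **Weight and waist were ignored in the power statement.** The article asserts sufficient power for both. It shows no figures, but the assertion is there.

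**Conclusion.** The concern holds as a multiplicity problem in the rule for the primary conclusion. Followed as written, the rule gives an overall false-claim rate of 14.3% if the endpoints are independent and about 11 to 13% under the assumed positive correlations. For false claims of benefit the figures are 7.3% and about 5.6 to 6.4%, against 2.5%. Either way the rate is two to three times the per-test level. The independence values follow from the article's own numbers; the lower ones depend on correlations it does not give. All of them assume that the programme affects none of the three endpoints.

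The point should be settled before analysis, because it governs the trial's main claim.

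**What to change.** In the Primary outcome section, delete the sentence "No adjustments to significance levels will be made for multiple testing". Replace it with Holm's procedure across the three between-arm differences at 12 months: the smallest p-value is compared with 0.05/3, the next with 0.05/2 and the largest with 0.05, stopping at the first failure. Holm needs no assumption about the correlations. Hochberg is an acceptable alternative, but it relies on suitable positive dependence among the tests. State that the adjusted-significant difference must favour the intervention, in line with the stated objective. This keeps the intention that any of the three endpoints can support the claim.

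The cost is power. For FPG at effect size 0.27 with 215 per arm, power falls from 80% to about 66% in the worst step, and the sample size section should report this. No extra participants are required if that loss is accepted.

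A fixed sequence that tests FPG first at 5%, then weight, then waist, would keep FPG's 80% power. It changes the question, because a null FPG result would block weight and waist however strong they were. It is an option only if the sponsor accepts that neither could then carry the claim alone.

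The Trial status section reports 134 women already randomized by June 4, 2013, and the trial is open. The change should therefore be made as a dated, justified amendment before any outcome analysis.
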